### Recruitment

Recruitment will take place in the Radiology Department of Yinchuan Women and Children Healthcare Hospital. Participants for the study will be recruited through WeChat advertising and posters in the infertility clinic. After patients arrive at the Radiology Department they will be screened with a free preliminary physical examination and a check against the inclusion/exclusion criteria. The potential participants will receive information about the aims, benefits, and latent risks of the study from the protocol designer. If the patients wish to participate, they will be asked to sign an informed consent form that they agree to participate in the study and are willing to let the protocol designer publicize the research results, including pictures. Participants are entitled to withdraw from the study at any time and this will not prejudice their subsequent treatment. The whole process of recruitment follows the principle of respect for autonomy.

### Randomization, allocation concealment and blinding

A simple random sampling method will be used in our study. Patients who are scheduled for HSG and meet the eligibility criteria will be randomly allocated into either the blank control group or the VR group at a 1:1 ratio. The randomization sequences will be generated in advance with a computerized random number generator (random.org). This is performed by a statistical expert who is not involved in this trial. A sealed opaque envelope will be used to store the randomization sequences of all allocations. The random number table will be kept confidential by the full-time secretary of this project. Baseline data will be recorded as close to immediately before the HSG procedure as possible. After baseline data collection, the allocation will be revealed. Blinding is not feasible.

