### Study participants

Women will be recruited into the study according to the following inclusion criteria: 1) indications for HSG including infertility, recurrent miscarriage, and other miscellaneous reasons [5]; 2) aged 20–45 years; 3) willing to participate in the study and sign informed consent; and 4) no signs of pain before HSG.

The exclusion criteria are: 1) use of antidepressants or sedatives; 2) presence of psychiatric disorders; 3) recent receipt of analgesics within 6 h; 4) allergy to contrast medium or iodine; 5) a recent history of acute pelvic inflammatory disease; 6) visual acuity <1.0 or hearing abnormity; 7) susceptible to motion sickness; 8) operator difficulty due to cervical adhesion or congenital variation, or completing the examination after multiple operations.

In the Radiology Department, the HSG procedure will be carried out on each weekday by two gynecology assistants (both female who have worked in the HSG room for >10 years). The results of the HSG will be analyzed by a Chief Radiologist (who has worked in the HSG room for >10 years). These two gynecology assistants will receive training from the protocol conceiver.

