Any observed adverse effects will be carefully evaluated and recorded by the investigators. The expected adverse effects include gastrointestinal adverse reactions (nausea, vomiting), adverse effects on the cardiovascular system (arterial hypotension and bradycardia) and any other discomfort (pallor, sudation, palpitation, dizziness, syncope). If any adverse effects take place, health care givers will administer corresponding treatment or nursing care. All severe adverse reactions and solutions during the procedure will also be noted. HSG results (both tubes patent, one or both fallopian tubes occluded and/or impaired patency) should be recorded and compared. The physiological indexes will be monitored in terms of treatment safety with an electronic manometer (OMRON, HEM-7120) and oximeter (PC-60B).

Participants’ demographic data, relevant medical history and baseline anxiety level, as well as pulse rate, digital monitoring of oxygen saturation and noninvasive monitoring of blood pressure, will be collected at baseline (T0) before the procedure. Patients will complete a series of assessment including three pain dimensions, physiological parameters (including pulse, blood pressure and oxygen saturation), anxiety level during HSG, satisfaction and acceptance of pain management and adverse reactions along with the immersion perception of the VR system (for the VR group only) immediately after the procedure (T1). HSG results and worst pain will be recorded 15 min (T2) after the procedure. To promote participant retention, every woman who completes all data collections will receive a free overall analysis of the HSG results by an experienced gynecologist.

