#### Secondary outcome measures

Secondary outcome measures include: 1) pain score of the cognitive component (by VAS), collected by asking patients to rate “How much time did you spend thinking about your pain during HSG?”, ranging from none of the time to all of the time; 2) pain score of the affective component (by VAS), collected by asking patients to rate “How UNPLEASANT was your pain during HSG?”, ranging from not unpleasant at all to excruciatingly unpleasant; 3) worst pain score within 15 min after HSG (by VAS); 4) anxiety score before/during HSG (by GRS), collected by asking patients to rate “How much ANXIETY did you have before/during HSG?”, ranging from none at all to extremely anxious; 5) patient satisfaction score with pain management (by GRS), collected by answering the question: “How satisfied were you with the holistic pain management during HSG?”, ranging from not satisfied at all to completely satisfied; 6) patient acceptance score of pain management (by GRS), collected by answering the question: “How receptive were you to overall pain management during HSG?”, ranging from not receptive at all to completely receptive; 7) immersion perception score of the VR system (by GRS), collected by answering the question: “To what extent did you feel like that you went into the virtual reality environment while experiencing VR?”, ranging from “I did not feel like I went into the virtual reality environment at all” to “I went completely into the virtual reality environment” (for the VR group only); 8) physiological parameters; 9) adverse effects; and 10) HSG results.

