### Statistical analysis

In this study, all data will be collected by a specialized researcher. A blinded statistician who is not involved in this trial will perform statistical analysis using SPSS version 22.0 (Chicago, IL, USA). A complete statistical analysis plan will be generated in advance by the trial statistician. All randomized participants should be included in the analysis, and missing data will be handled using multiple imputation. Data will be analyzed initially on an intention-to-treat basis. For comparing the primary outcome between the two parallel groups, additional per-protocol analysis will be performed, and reasons for any protocol violations will be reported. We will consider all *P* values <0.05 to be statistically significant.

Descriptive statistics will be used to describe the demographic features by means (SD), medians (interquartile ranges; minimum to maximum), and proportions (exact binomial 95% confidence intervals). A *t* test will be applied to determine the differences between the primary outcome. Secondary outcomes such as the amount of time spent thinking about pain, pain unpleasantness, worst pain within 15 min after HSG, anxiety, satisfaction, and acceptance with pain management will use *t* tests or Mann–Whitney tests. Chi-squared tests or Fisher’s exact test will be used for HSG results and adverse reactions. When comparing the physiological parameters, the repeated measures analysis of variance will be used. Pearson correlation analysis will be used to analyze the relationship between immersion perception score of the VR system and the three pain dimensions.

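### Blinding is ruled out without exception, although the statistician is blinded and the radiologist who reads the HSG could probably be masked too

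*Protocol article*

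**What the plan says.** The protocol article's section Randomization, allocation concealment and blinding ends with "Blinding is not feasible". The sentence names no role and no outcome.

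Other sections bear on it:

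- **Analyst.** Statistical analysis: "A blinded statistician who is not involved in this trial will perform statistical analysis using SPSS version 22.0".
- **Operators.** Study participants: "the HSG procedure will be carried out on each weekday by two gynecology assistants".
- **Reader.** Study participants: "The results of the HSG will be analyzed by a Chief Radiologist". Nothing is said about what this reader knows of the allocation.
- **Status of the outcome.** Secondary outcome measures closes its list with "8) physiological parameters; 9) adverse effects; and 10) HSG results".
- **Categories.** Measurements: "both tubes patent, one or both fallopian tubes occluded and/or impaired patency) should be recorded and compared".
- **Test.** Statistical analysis: "Chi-squared tests or Fisher’s exact test will be used for HSG results and adverse reactions".

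The Limitations section takes up the lack of blinding only as a reason why women might under-report pain on the VAS. It does not consider the image reading.

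**The concern.** Women who wear a headset, and staff who work beside them, cannot be masked. That reason does not carry over to a person who reads the pelvic images, and the article gives no other reason. Followed as written, the sentence leaves the HSG reading open to knowledge of the arm.

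This matters because the result is not just counted. Deciding whether a tube shows impaired patency takes judgement, and the procedures section itself accepts that tubal spasm can look like obstruction on the images. A reader who knows the arm and the hypothesis could lean one way on borderline cases, and so create or hide a group difference in an outcome that will be formally tested. The HSG result also touches the aim stated in the Background, of learning how pain relief affects the ease of performing HSG for diagnosis.

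**Working it through.** The plan gives no figure on this point, so the check is mainly a comparison of sections.

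**1. Does the blinding sentence hold for every role?** No. It is unqualified, but Statistical analysis has a blinded statistician. The two places can be reconciled only by saying who is and who is not blinded.

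**2. Is the reader a different role from the operators?** Yes. Study participants assigns the procedure to two gynecology assistants and the reading to a Chief Radiologist.

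**3. Would the images reveal the arm?** Probably not. Under Hysterosalpingography procedures, the images are taken to assess the uterus and tubes. Under Virtual reality prototype and Interventions, the device is a head-mounted display with hand controllers. This is an inference from those sections; the article does not say it.

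**4. Is the outcome compared between arms?** Yes. It is item 10 of 10 secondary outcomes, is to be compared, and has a named test.

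**5. Is masking of the reader stated, or ruled out for a reason?** Neither, in any section.

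**6. Is it clear how the reading is done?** No. Images are taken at intervals under fluoroscopy and the result is recorded 15 min after the procedure. The article does not say whether the radiologist attends or reads stored images.

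**7. What size could the bias have?** The documents give no rate at which knowledge of the arm changes a reading, so any figure is an assumption. Take the 95 women per group from Sample size determination, and suppose that the changed readings all fall in one arm and all go one way:

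| Assumed share of readings changed | Women reclassified | Shift in group difference |
|---|---|---|
| 5% | 0.05 × 95 = 4.75 | 5 percentage points |
| 10% | 0.10 × 95 = 9.5 | 10 percentage points |

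Changes that partly cancel within the arm would give less, and a reader who ignores the arm would give zero.

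**8. Does the point touch the main design?** No. The sample size rests on the worst pain score. The article's formula with its own inputs, 4 × (z₀.₉₇₅ + z₀.₉₀)² × 1.72² / 0.89², gives 156.98 against the stated 157.02, and 79 per group either way. Masking the reader enters none of these terms.

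**The case against.** The strongest reply is that the sentence comes straight after the statement that allocation is revealed, and that Limitations speaks of the treatment condition as unblinded. Its natural meaning would then be that participants and procedure staff cannot be masked, which is true. Nothing says that the radiologist knows the arm, and a condensed article may leave the masking of an image reader to the full protocol. This has weight: a reader might infer that the reading is certainly unmasked, and the article does not show that. But the article does more than stay silent. It makes an unqualified statement that does not fit its own blinded statistician and that, taken literally, includes the image reader.

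Other parts of the reply stand and limit the point:

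- A reader might infer that the trial has no blinding at all. The blinded statistician contradicts that.
- A reader might infer that masking is free. The documents do not support that. How the radiologist works is not described, the reading appears to serve as the woman's own diagnostic result, and Data storage assigns the study ID when data are entered, with no sign that images carry it.
- A reader might infer that a masked reading would make the HSG result independent of bedside staff. It would not. The procedure staff place the catheter and carry out the examination with the arm in view, so the images themselves come from unmasked hands.
- No reason is given why a radiologist would favor either arm, and the 5% to 10% range has no source in the documents.

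**Conclusion.** The point holds in a limited form. The blinding sentence is too broad for the plan's own arrangements, and it passes over a reader who could probably be masked for a judged secondary outcome that is compared between arms. The result is an avoidable risk of bias of unknown size. The shift of 5 to 10 percentage points only illustrates what one-sided changes in 5% to 10% of one arm's readings would do.

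The conclusion assumes that the images do not show the arm and that the reading can be kept apart from the procedure. The first is likely from the description; the second is not settled by it. Even if both hold, masking protects only the reading step.

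The matter is minor, a cheap improvement. It concerns one of ten secondary outcomes and has no bearing on the self-reported primary outcome, the sample size, the alpha or the power.

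**What to change.** Replace the one blinding sentence with a statement by role, for example:

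> *Participants and procedure staff are not blinded. The statistician is blinded. The Chief Radiologist classifies the HSG images without knowledge of allocation, and the reading request carries no arm information.*

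This also reconciles the blinding section with Statistical analysis. If the radiologist has to attend the procedure, say so and add unmasked reading of the HSG result to Limitations.

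The cost is a short text change and the removal of arm information from the request. The small downside is that the reading must be kept apart from the procedure room, which may mean some change in workflow.

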### Virtual reality prototype

The immersive VR prototype has been constructed by combining commercial, advanced, off-the-shelf components. The prototype consists of an HTC VIVE VR system and a VIVE-ready computer with a head-mounted display helmet with noise-reducing headphones, two wireless controllers and two base stations included with the HTC VIVE VR system. The head-mounted display helmet will be linked to a desktop computer (Dell OptiPlex 7050, Windows 10 64-bit operating system, Intel® Core™ i7-7700 processor, 3.60 GHz central processing unit, 8.0 GB installed random-access memory, Intel® HD Graphics 630 video card) with Steam VR software. The VR environment comes from Zamer which is a software platform to distribute VR content (www.zamertech.com). Under VR treatment, participants can travel on a canoe slowly through three magic virtual scenes (Fig. 3). Music in the virtual scenes is an adapted opera. The immersive VR prototype developed by HTC will be adapted to the HSG room in the Radiology Department. The main researchers will be trained in proficiency with VR intervention in the Ningxia Medical University Innovation and Entrepreneurship Park of Health and Medicine.

**Fig. 3 Fig3:**
[figure not shown]
Screenshots of the virtual scenes provided for participants in the virtual reality group. **a** The land of magma. **b** The frozen ground. **c** A flowering tree in the violet world

### Hysterosalpingography procedures

HSG will be scheduled by gynecologists between 3 and 7 days after the end of menstruation. Any history of iodine allergy and unfavorable pregnancy will be obtained. The colloidal gold test paper will be used to exclude early pregnancy. In the preoperative waiting room, patients arranged for HSG will receive routine care without any analgesia provided. Atropine (0.5 mg) will be administered intramuscularly approximately 30 min before HSG to prevent fallopian tube spasm which could lead to false obstruction during the imaging examination during HSG.

After placing the patients in the lithotomy position on the fluoroscopic table, the gynecology assistants help them to flex and separate the thighs to fully expose the vulva and then perform vaginal irrigation for local cleaning with antiseptic 1% chlorhexidine solution. After disinfecting the vulva with a standard 2000 mg/L iodophor solution, a sterile bivalve speculum is introduced into the vagina to visualize the uterine cervix. A 4-mm sterile uterus radiography balloon catheter is inserted through the cervical canal and a tenaculum used to hold the cervix only if it is difficult to insert. The gynecology assistant injects 2 mL air into the aerocyst in the uterus radiography balloon catheter. After filling the balloon, it is gently pulled back to fix the catheter in the internal cervical orifice to prevent contrast leakage. A water-based iodine contrast medium (Omnipaque 300; GE Healthcare, Shanghai, China) in volumes of 5–15 ml is instilled through the uterus radiography catheter with fluoroscopic x-ray images obtained intermittently to assess the uterus and fallopian tubes. The whole procedure lasts about 20 min. At the end of the operation, the cannula and instruments are removed and the patient remains under observation for 15 min in the Radiology Department before discharge.

### Interventions

In the blank control arm, gynecology assistants will perform the whole procedure as they usually would. In the VR group, the immersive VR system will be provided (Fig. 4). After placing the patient in the lithotomy position, the trained investigator will help the patient wear the specific helmet and teach them how to interact with the virtual world through gaze-based tracking and the wireless controllers. The gynecology assistant will carry out the relevant operation 2 min later. VR distraction will be applied during the whole procedure. Patients in the VR group will be asked how many virtual scenes they ‘enter’ to monitor adherence to intervention protocols.

**Fig. 4 Fig4:**
[figure not shown]
A patient undergoing a hysterosalpingography procedure on the fluoroscopic table ‘enters’ the immersive virtual world

### Measurements

Demographic data (age, nationality, education, occupation) and physiological parameters, including pulse rate, blood pressure and oxygen saturation, will be recorded by the investigator. In order to evaluate gynecologic and pelvic pain-associated histories, patients will be examined and their relevant medical history will be collected (duration of infertility, primary or secondary infertility, vaginal or cesarean delivery, prevalence of dysmenorrhea and dyspareunia, history of dilatation and curettage, HSG, and abdominal surgery or infection). Other indexes regarding pain score, baseline anxiety level, anxiety level during HSG, adverse effects, patient satisfaction and acceptance of pain management, as well as the immersion perception of the VR system, will be recorded by the researcher.

Cognition and emotion are important factors known to regulate pain perception in clinical settings and laboratories [19]. Sensory and affective pains are separate dimensions of the pain experience and can be measured respectively [20]. Thus, like other clinical VR studies [15, 21], subjects will be asked to complete three self-assessment pain outcomes in this study: the sensory pain dimension (worst pain), the cognitive pain dimension (amount of time spent thinking about pain) and the affective pain dimension (pain unpleasantness). Participants will respond to questions about worst pain, amount of time spent thinking about pain, and unpleasantness they experience during HSG by using a visual analog scale (VAS) (range = 0 to 10). VAS is a widely used self-report instrument in younger adults [22]. The extremes of the 10-cm line VAS are “no pain at all/none of the time/not unpleasant at all” and “worst pain possible/all of the time/excruciatingly unpleasant” [23–25]. Moreover, baseline anxiety level, anxiety level during HSG, patient satisfaction and acceptance of pain management, and the immersion perception of the VR system will be measured using a graphic rating scale (GRS) labeled from 0 to 10 labeled. Gracely et al. [20] have proved ratio scale measures such as the GRS to be highly reliable.

Any observed adverse effects will be carefully evaluated and recorded by the investigators. The expected adverse effects include gastrointestinal adverse reactions (nausea, vomiting), adverse effects on the cardiovascular system (arterial hypotension and bradycardia) and any other discomfort (pallor, sudation, palpitation, dizziness, syncope). If any adverse effects take place, health care givers will administer corresponding treatment or nursing care. All severe adverse reactions and solutions during the procedure will also be noted. HSG results (both tubes patent, one or both fallopian tubes occluded and/or impaired patency) should be recorded and compared. The physiological indexes will be monitored in terms of treatment safety with an electronic manometer (OMRON, HEM-7120) and oximeter (PC-60B).

Participants’ demographic data, relevant medical history and baseline anxiety level, as well as pulse rate, digital monitoring of oxygen saturation and noninvasive monitoring of blood pressure, will be collected at baseline (T0) before the procedure. Patients will complete a series of assessment including three pain dimensions, physiological parameters (including pulse, blood pressure and oxygen saturation), anxiety level during HSG, satisfaction and acceptance of pain management and adverse reactions along with the immersion perception of the VR system (for the VR group only) immediately after the procedure (T1). HSG results and worst pain will be recorded 15 min (T2) after the procedure. To promote participant retention, every woman who completes all data collections will receive a free overall analysis of the HSG results by an experienced gynecologist.

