## Methods/design

### Study design

The primary objective of this single-center, parallel-group, randomized controlled trial is to find out the clinical analgesic effect of VR intervention in patients during HSG compared with a blank control group. The secondary objectives of this trial include comparing the anxiety level during HSG between the two groups, evaluating the safety of clinical use of VR by recording adverse effects and physiological indexes, assessing patient acceptance for the nonpharmaceutical analgesia therapy and investigating the satisfaction of patients with VR.

The trial has been approved by the Institutional Ethics Committee of Ningxia Medical University (reference no. 2018–233). This randomized controlled trial has been registered in the Chinese Clinical Trial Registry (ChiCTR1900021342). The whole study design is illustrated in Fig. 1. Additionally, a Standard Protocol Items: Recommendations for Interventional Trials (SPIRIT) figure for the schedule of enrolment, interventions, and assessments is presented in Fig. 2. We will conduct the protocol of this trial according to the SPIRIT guidelines (see Additional file 1).

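### The text schedules a prompted adverse-effect assessment at T1 only, leaving the 15-minute observation period to unprompted staff observation under an adverse-effect window that the sections do not fix consistently

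*Protocol article*

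**What the plan says.** Study design in the protocol article makes safety a secondary objective, to be met by "evaluating the safety of clinical use of VR by recording adverse effects and physiological indexes". Secondary outcome measures closes its list with "8) physiological parameters; 9) adverse effects; and 10) HSG results" and attaches no time point to adverse effects. Statistical analysis compares adverse reactions between the arms by a chi-squared or Fisher's exact test.

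Measurements assigns items to time points. The set completed at T1, immediately after the procedure, includes "satisfaction and acceptance of pain management and adverse reactions along with the immersion perception of the VR system". For the later contact the sentence is "HSG results and worst pain will be recorded 15 min (T2) after the procedure".

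The same section has two general recording sentences. One is "Any observed adverse effects will be carefully evaluated and recorded by the investigators", with no window. The other is "All severe adverse reactions and solutions during the procedure will also be noted".

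Under Hysterosalpingography procedures, "the patient remains under observation for 15 min in the Radiology Department before discharge". The Abstract says in general terms that outcomes are followed at baseline, just after HSG and 15 minutes after it. Fig. 2 holds the schedule of assessments, but its content is not available here.

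**The concern.** An outcome that is tested between arms needs one stated window and the same method of ascertainment throughout it. Here the text appears to use two methods. Up to T1, each woman is assessed for adverse reactions as part of a scheduled set. Between T1 and T2, the text provides only for recording what investigators happen to observe.

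The second method is weaker for symptoms that have to be asked about. It also depends more on the observer, in a trial where the protocol says blinding cannot be done. At stake is how complete, and how comparable between arms, the data for the safety objective are. The protocol already treats this quarter of an hour as relevant for pain: the worst pain score within it is a secondary outcome in its own right. Adverse effects get no matching definition.

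**Working it through.** The documents give no figure on this point, so the check sets the sections side by side.

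**What is scheduled at each time point in Measurements**
- T0: demographic data, history, baseline anxiety, pulse, oxygen saturation, blood pressure.
- T1: three pain dimensions, physiological parameters, anxiety during HSG, satisfaction, acceptance, adverse reactions, and immersion (VR arm only).
- T2: HSG results and worst pain.

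Adverse reactions therefore appear once in the scheduled lists, at T1. Physiological parameters, the other safety measure, appear at T0 and T1 but not at T2.

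**What covers the time from T1 to T2**
- The woman is still present, because she is observed for 15 minutes before discharge.
- She is spoken to at T2, because she rates her worst pain.
- The sentence on any observed adverse effect has no end point, so it can cover this period.
- No sentence in the text says that she is asked about adverse effects at T2.

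**Which expected reactions depend on being asked or measured**

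Measurements lists the expected effects. Vomiting, pallor, sweating and syncope can be seen by staff. Nausea, palpitation and dizziness are mainly known if the woman reports them. Hypotension and bradycardia need a measurement, and none is listed at T2. The general sentence is thus adequate for part of the list and weak for the rest.

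**Consistency of the window**
- Abstract: all outcomes, adverse effects among them, in general at T0, T1 and T2.
- Measurements: scheduled at T1; any observed effect without limit; severe reactions mentioned for the procedure.
- Secondary outcome measures: no time point.
- Limitations: describes the participants' questionnaire data on side effects as relating to the HSG itself.

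These do not contradict each other outright, but they do not define a single window either.

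**Why no size can be given**

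Let p be the proportion of women in an arm whose first reaction starts after T1, and r the proportion of those picked up by staff without prompting. The proportion of women wrongly counted as event-free is then p × (1 − r). The distortion of the between-arm difference is the difference between the two arms' values of p × (1 − r). The documents give neither p nor r for either arm, so neither quantity can be computed or signed.

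**The case against.** The strongest reply is that the protocol never says adverse effects are collected at T1 alone. The sentence on any observed adverse effect is unlimited, observation continues for 15 minutes, the Abstract names a 15-minute time point for outcomes in general, and Fig. 2 may list adverse effects at T2. All of this stands. A reader might infer that reactions after T1 are not collected and are lost; the text does not support that. A faint or a vomiting episode during observation would fall under the general sentence.

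A reader might also infer that severe reactions count only if they occur during the procedure. The sentence on severe reactions says they will also be noted, which adds to the general rule and does not narrow it.

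A third tempting inference is that under-recording would favour VR, because after-effects of the helmet can arise only in that arm. The documents do not establish this. The schedule is the same in both arms, the listed reactions are not presented as specific to VR, and women susceptible to motion sickness are excluded. VR runs during the procedure and T1 follows it, so effects around removal of the helmet may already fall within T1.

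Finally, form detail is often left to a full protocol. That carries limited weight here, because the article does set out what is assessed at T1 and T2. If Fig. 2 or a fuller document lists adverse effects at T2, the Measurements text should be brought into line with it.

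**Conclusion.** The point holds in a limited form. In the text, the only scheduled, prompted adverse-effect assessment is at T1. Symptoms that start in the 15-minute observation period are left to unprompted recording by unblinded staff and may be under-recorded. The adverse-effect window is not stated consistently across the Abstract, Measurements and Secondary outcome measures.

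The size of any under-recording and its direction between arms are unknown. The conclusion concerns one of ten listed secondary outcomes, though it is one that carries the safety objective. It does not touch the primary outcome or the sample size. It rests on the text as printed, with Fig. 2 unread, and on the assumption that some of the expected reactions can begin after T1. The change is worth making because the contact at T2 already exists.

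**What to change.** 1. In Measurements, add the adverse-effect checklist used at T1 to the T2 assessment in both arms, asked in the same words.
2. In Secondary outcome measures, define the adverse-effect outcome, including severe reactions, as any event from the start of the procedure to T2.
3. Align the Abstract, Measurements and Secondary outcome measures with that definition, and check Fig. 2 against it.

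The cost is one extra block on the existing T2 form and about a minute per woman, with no added visit and no change to the sample size. Trial status reports 22 women already recruited. Any woman assessed before the change would have prompted data to T1 only, and the report should say so.
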